#### Secondary end points

The secondary end points will be:

1. Crude (PCR uncorrected) adequate clinical and parasitological response ratio at day 28 (PCR-uncorrected ACPR)
2. Cure ratios at days 42, 63, and 84 (PCR-corrected and PCR-uncorrected ACPR)
3. Fever clearance time (FCT)

Fever clearance time will be defined as the time (in hours) from the start of a patient’s treatment to the first consecutive axillary temperature measurements below 37.5°C (body temperature <37.5ºC for at least 48 hours).

1. Asexual parasite clearance time (PCT)

Asexual parasite clearance time will be defined as the time (in days) from the start of a patient’s treatment to 2 consecutive negative blood slides (collected at different days).

1. Gametocyte carrier rates and geometric mean densities (excluding negatives) will be compared on days 7, 14, 28 and 42.
2. Changes of haemoglobin (Hb) concentration from day 0 to days 28, 42, 63, and 84.
3. Safety profiles of the two treatments.
4. Adverse events, vital signs, blood chemistry and haematology, electrocardiogram (ECG) will be monitored and changes in relevant laboratory parameters will be assessed.
5. Rate of PCR-confirmed reinfections
6. Plasma concentration of piperaquine at time of asexual parasite reappearance.
7. Detection of subpatent asexual parasitaemia on day 7 **and day 14**
8. **Assessment of the relationship between *var* gene transcription patterns and late asexual parasite recurrence**

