## Recruitment and trial procedures

The parents or guardians of paediatric patients aged 6-59 months who present to the Pingilikani Health Centre with symptoms suggestive of malaria and a documented, uncomplicated *P. falciparum* infection with an asexual parasite density of 2,000–200,000 parasites/µL, will be informed by the health care facility staff about the ongoing malaria clinical trial. They will be requested to freely consent to let their child participate in the trial. Unwillingness or inability to participate will result in the prescription and administration of the local standard treatment regime for uncomplicated *P. falciparum* malaria (currently 4 mg/kg/day of amodiaquine for 3 days). A screening record will be maintained at the site to log all patients considered as potential subjects into the study, and a recruitment record to log all patients recruited into the study.

The parents or guardians who express interest in participation of their child in the study will receive detailed explanations about the trial from the study staff. Specifically they will be informed that the safety, tolerability and efficacy of two antimalarial drugs will be compared and that their child will be randomly assigned to receive treatment with one of the two drugs (by chance). Finally, they will be asked to sign the informed consent form (see Appendix IV). The study will be explained in the patient’s preferred language (English, Swahili, Giryama), and written informed consent shall be obtained on approved forms (accuracy of translation to be checked by back-translating into English).

At enrolment, children will be assigned a sequential study number. During the first 3 study days (days 0-2) patients will be either be admitted for observation and administration of study medication or managed as outpatients requiring home visits for supervised administration of study drugs at nighttime. Parents/guardians will then be encouraged to return to the clinic for follow up assessments on days 3, 7, 14, 21, 28, 35, 42, 63, and 84 and on any unscheduled day if the child is not well. Compensation for transport to and from the clinic will be provided. All medication will be administered under observation by an authorised member of the study team (physician, clinician, or study nurse).

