1. PCR

A blood sample will be collected on filter paper (grade 1) for parasite genotyping.

1. Blood Slide

A thick and thin blood smear will be obtained from the subject to verify the presence of *P. falciparum* and to determine asexual and sexual parasite densities. Thick and thin blood films will be prepared, dried and stained with Giemsa stain according to standard operating procedures.

Parasite density will be calculated by counting the number of asexual parasites per 200 leukocytes in the thick blood film, based on an assumed leukocyte count of 8,000 /µl by light microscopy at 1000x magnification. One hundred high-powered fields (HPF) will examined (independent of presence or absence of asexual parasite stages). The parasite density per µL will be calculated using the following formula: numbers of parasites/µl = number of parasites counted x 8,000/number of leukocytes counted

1. Laboratory Tests

Blood haemoglobin, red blood cell count, total leukocyte count, differential count (neutrophils, basophils, eosinophils, monocytes, lymphocytes) and platelet count.

Total bilirubin, ALT and creatinine will be measured. **Parasite RNA will be analysed for variant gene expression patterns.**

1. Administration of the study drugs

For details see chapter 7 (Investigational product(s) & concomitant medications and non-drug therapies).

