## Patient follow-up

Patients will be monitored daily until parasite and fever clearance is achieved. Active follow-up will be on days 3 and 7, then weekly on days 14, 21, 28, 35, 42, 56, and 63 and finally again on day 84; all subjects will be seen on any day between 0 and 84 upon request. The patient-specific CRF will be used to record clinical and laboratory data on each on these visits.

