### Secondary end point analyses

#### Secondary efficacy end point analyses

Normally distributed variables will be summarized by calculating means and standard deviations (SD) and compared with parametric tests (unpaired and paired Student’s *t* or analysis-of-variance (ANOVA) tests as appropriate). Non-normally distributed variables will be summarized by median and interquartile ranges (IQR) or geometric means and 95% confidence intervals. Comparisons will be made with nonparametric tests (unpaired and paired Wilcoxon or Kruskal-Wallis rank tests as appropriate). The Fisher’s exact test will be used to assess differences in categorical outcome variables between the cohorts. The statistical significance level will be set to 5%.

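### Parasite clearance time would be compared without adjustment for day 0 parasite density, which gives up some precision on this secondary end point

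*Protocol*

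**What the plan says.** Protocol 12.3.2.1 (Secondary efficacy end point analyses) sets one general rule for all secondary efficacy variables. Normally distributed ones are "compared with parametric tests (unpaired and paired Student’s *t* or analysis-of-variance (ANOVA) tests as appropriate"). For the others, "Comparisons will be made with nonparametric tests (unpaired and paired Wilcoxon or Kruskal-Wallis rank tests as appropriate"). Categorical outcomes go to Fisher's exact test. The section names no covariate and does not single out parasite clearance time.

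Clearance time is listed in 10.4.1.2 (Secondary end points): "Asexual parasite clearance time will be defined as the time (in days) from the start" of treatment to two consecutive negative slides taken on different days. Section 10.6 (Patient follow-up) adds: "Patients will be monitored daily until parasite and fever clearance is achieved".

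On the baseline value, 10.5 (Recruitment and trial procedures) admits children with "an asexual parasite density of 2,000–200,000 parasites" per µl. The day 0 smear in 10.5.1.1 is taken "to determine asexual and sexual parasite densities", by "counting the number of asexual parasites per 200 leukocytes in the thick blood film" with an assumed leukocyte count of 8,000/µl. Randomisation (11.1.3) is blocked, with no stratification by density mentioned.

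**The concern.** A whole-day outcome taking only a few values will in practice go to the rank test, and either branch of the rule is unadjusted. The time a child needs to reach a negative slide depends on how fast parasites fall and on how many there were at the start. The second quantity is known for every child before treatment. Leaving it out keeps its contribution in the error term, so a real difference in clearance speed is somewhat more likely to be missed.

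Speed of parasite clearance is one of the stated secondary objectives. The adjustment needs no new data, and it is more credible if named before the data are seen than if chosen afterwards.

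**Working it through.** **No figure to reproduce.** The protocol gives no power, standard deviation or sample size for clearance time. Its 235 evaluable children per group (10.4.2) belong to the primary end point and serve below only as a group size.

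**Step 1: why density is prognostic.**
- Entry range: 200,000 / 2,000 = 100-fold.
- One parasite per 200 leukocytes corresponds to 8,000 / 200 = 40/µl.
- With first-order clearance (an assumption), time to the limit = ln(density / limit) / rate.
- Limit 40/µl: ln(2,000/40) = ln 50 = 3.91 and ln(200,000/40) = ln 5,000 = 8.52; ratio 2.18.
- One hundred fields are also examined, so the working limit may be lower. At an assumed 10/µl: ln 200 = 5.30 and ln 20,000 = 9.90; ratio 1.87.

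At an equal clearance rate, the extremes of the entry range therefore differ about twofold in time to clear.

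**Step 2: share of variance and power.** Trials were simulated with 235 per arm, slides at 24, 48 and 72 h, a 10% slower clearance rate in one arm and a 5% two-sided test. The unadjusted Wilcoxon test was compared with a regression of ranks on arm and log day 0 density (rank ANCOVA). Median rates, between-child coefficients of variation (CV) and the density distribution are assumptions.

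Log-uniform density, limit 40/µl, 1,500 trials per setting:

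| Median rate (per h) | CV of rate | Wilcoxon | Rank ANCOVA | Gain (points) |
|---|---|---|---|---|
| 0.17 | 20% | 92% | 99% | 7 |
| 0.17 | 30% | 77% | 89% | 12 |
| 0.17 | 50% | 51% | 60% | 9 |
| 0.22 | 20% | 87% | 98% | 11 |
| 0.22 | 30% | 76% | 88% | 12 |
| 0.22 | 50% | 50% | 57% | 7 |

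Day 0 density explained 15% to 41% of the variance of ranked clearance time. A repeat with new random numbers agreed to within about three points; the 0.22/h, 30% setting came out at 74% v 88%, a gain of 14, so the top of the range is approximate.

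Less favourable inputs:
- Log-uniform density, limit 10/µl: 11% to 33% of variance, gain 5 to 8 points.
- Truncated lognormal density (median 25,000, log-SD 0.9), limits 10 and 40/µl, rate 0.17/h, 400 trials per setting: 5% to 17% of variance, gain about 1 to 8 points.

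A simulation built differently (250 per arm, reads on days 1, 2, 3 and 7, a lag of 0 to 8 h, median half-life 2 to 4 h) gave a rank correlation of 0.29 to 0.58 between density and clearance time. Squared, that is 0.08 to 0.34, inside the same range.

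**Step 3: equivalent sample size.** Relative size = 1 / (1 − R²). For R² = 0.05 it is 1 / 0.95 = 1.05; for R² = 0.41 it is 1 / 0.59 = 1.69. Adjustment is worth between 5% and 69% more children, depending on the assumptions.

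**Step 4: validity.** With no drug difference, both tests rejected in 4.6% to 5.5% of trials in the first simulation. The unadjusted test rejected in about 4% to 6% in the differently built one.

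**The case against.** The strongest reply is that covariates for one secondary end point are ordinary content for a statistical analysis plan, which may exist and is not shown, and that 12.3.2.1 is generic and leaves the choice of test to what is appropriate. That limits the weight of the point: it is an inference that clearance time falls under the rule. It does not remove it, because this is the only rule the protocol gives for these variables and every test in it is unadjusted.

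The assumptions also deserve suspicion. The entry limits are not a distribution, and a log-uniform shape spreads density widely; a more peaked one cuts the gain to a few points in some settings. This stands, and is why the range is wide.

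Three stronger readings are tempting but unsupported:
- *Density fixes the clearance time.* It is one determinant. Rates vary between children, time is read in whole days, and even the most favourable setting leaves 59% of the variance unexplained.
- *A chance imbalance in density would bias the comparison.* Under randomisation that risk already lies within the test's 5% error, as Step 4 shows.
- *Children rescued before clearing are dropped, which removes the slowest responders.* No section says so, and a rank test can hold them at the worst rank. The protocol is merely silent. They should also be few, given the 95% cure assumed for the reference arm.

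A grouped-time complementary log-log model might seem the natural remedy, but it showed no more power than rank ANCOVA in any setting checked. With lognormal density and a CV of 50% it was no better than the plain Wilcoxon test (52% v 55% at 40/µl, 56% v 59% at 10/µl, simulation error about 2.5 points).

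**Conclusion.** The point holds as a matter of efficiency. The comparison of clearance time implied by 12.3.2.1 is valid but ignores a prognostic value measured in every child. Under the assumed density shapes, detection limits of 10 to 40/µl and rate CVs of 20% to 50%, day 0 density accounts for about 5% to 41% of the variance of ranked clearance time, and using it adds about 1 to 12 points of power against a 10% slower rate. None of those inputs is given in the protocol except the entry range and the counting rule, so the direction is secure and the size is not. Rank ANCOVA did not lose power against the Wilcoxon test in the settings with a 10% slower rate. The end point is secondary, no power is claimed for it, and the primary conclusion does not depend on it. This is a modest, inexpensive improvement, not the correction of an error.

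**What to change.** In 12.3.2.1, or in the analysis plan if one is written, state that:

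- parasite clearance time is compared between arms by rank ANCOVA with treatment and log10 day 0 asexual density;
- a child given rescue treatment before clearing stays in this analysis at the worst rank;
- the unadjusted Wilcoxon test is reported as a supportive analysis;
- a grouped-time complementary log-log model with the same two terms may be added as a sensitivity analysis.

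The cost is wording and a little more analysis work; no new data are needed. The one drawback is that an adjusted rank comparison has a less simple effect summary, which can be met by showing the proportion cleared by day 1, 2 and 3 in each arm beside it.

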#### Safety and tolerability

The ITT population will be considered for the following analysis.

Adverse Events (AEs) will be tabulated according to degree of seriousness, time of treatment at AE onset, severity, relation to study drug, action taken, if any, and final outcome.

Vitals signs and ECG will be analysed descriptively.

ECG results will be classified as normal and abnormal. The evaluation of ECG and QT interval will be done according to the European Medicines Evaluation Agency (EMEA) directive “Point to consider: the assessment of the potential for QT interval prolongation by non-cardiovascular medicinal products”. EMEA (CPMP), London 17/12/1997 (CPMP/986/96).

# TIME FRAME/DURATION OF THE PROJECT

We plan to carry out the study from JULY 2005 to December 2007 (time from start from enrollment to last follow-up visit). Data analysis and report writing will commence in January 2007. We intend to submit the results of this study by April 2008 as an independent report to an international peer-reviewed scientific journal.

# BUDGET

*COE = cost of employment (includes benefits, e.g. gratuities, insurance and medical cover); TCOE = total cost of employment (includes annual salary and benefits)

The cost per patient is calculated by dividing the sum of the subtotals from the following budget lines: staff costs, clinical costs, transport costs, admission costs/meals and stationery/freight/communications (USD 201,998.30) by the total number of patients (n=500).

# ETHICAL CONSIDERATIONS

This study will be conducted in accordance with Good Clinical Practice/International Conference on Harmonisation (GCP/ICH) guidelines and all applicable regulatory requirements, including, the latest revision of the Declaration of Helsinki from the year 2000. A complete and fully referenced set of Standard Operating Procedures (SOP) directs the conduct of the clinical study. This set of SOP is linked to the SOPs for the KEMRI clinical laboratories at Kilifi District Hospital representing a comprehensive network of quality assurance measures.

## National Ethical Committee

The present protocol will be submitted to the Kenyan national ethical committee for approval. Copies of the written approval will be remitted to all partners involved in the study. During the study, the investigators are committed to inform the ethical committee of any emergent problems, serious adverse events, or protocol amendments.

## Informed consent

Informed consent will be obtained before the subject can participate in the study. Female patients of child bearing potential will first be required to give a written consent for a pregnancy test before consideration for possible participation in the study. The contents and process of obtaining informed consent will be in accordance with all applicable regulatory requirements. The consent form generated by the investigator with the assistance of EDCTP/WHO, should be approved (along with the protocol) by the ERC/IRB and be acceptable to EDCTP/WHO. Consent forms must be in a language fully comprehensible to the prospective patient, their relatives, guardians or, if necessary, legal representatives. Informed consent shall be documented by the use of a written consent form approved by the ERC/IRB and signed by the patient or the patient's legally authorised representative.

## Study Monitoring

An independent monitor (MDS Pharma, Johannesburg, South Africa) will verify the best conduct of the study through frequent contacts by phone and in person with the Principal Investigator and site staff, in accordance with the Standard Operating Procedures and Good Clinical Practice, with the purposes of facilitating the work and attaining the objectives of the study.

## Data Safety Monitoring Board (DSMB)

An independent Data Safety Monitoring Board will review relevant efficacy data and all safety data.

## Quality Assurance (QA)

A random sample of the blood smear readings and PCR analysis will be checked for accuracy by an independent laboratory.

# EXPECTED APPLICATION OF RESULTS

This is a pivotal phase III study on the combination of dihydroartemisinin-piperaquine, aimed at evaluating the efficacy and safety of the newly manufactured GMP batch of the co-formulated tablet in the treatment of African children with uncomplicated *P. falciparum* malaria. If dihydroartemisinin-piperaquine proves to be efficacious and safe, it will provide a valuable addition to the therapeutic armamentarium for the treatment of malaria in Kenya. Of particular interest is that this antimalarial has added advantages of being a fixed-dose artemisinin-based combination chemotherapy that is relatively inexpensive and has a simple dosage regimen. The results of this study will provide data for the registration of this promising antimalarial combination as a prerequisite for its potential use as a first-line antimalarial drug.

# APPENDIX I

**Criteria for Severe Malaria/Danger Signs**

**Severe Malaria**

- Unarousable coma *(if after convulsion, > 30 min)*
- Repeated convulsions *(> 2 within 24 h)*
  - Severe anaemia *(Hb < 5.0 g/dL)*
  - Respiratory distress *(laboured breathing at rest)*

**Danger Signs**

- Recent convulsions *(1-2 within 24 h)*
- Altered consciousness  *(confusion, delerium, psychosis)*
- Lethargy
  - Unable to drink or breast feed
  - Vomiting everything
  - Unable to stand/sit due to weakness
